## Abstract

**Background:**

We hypothesise, based upon the findings from our previous trial, that the addition of co-trimoxazole to standard therapy is beneficial to patients with moderate to severe idiopathic pulmonary fibrosis (IPF). We aim to investigate this by assessing unplanned hospitalisation-free survival (defined as time from randomisation to first non-elective hospitalisation, lung transplant or death) and to determine whether any effect relates to changes in infection and/or markers of disease control and neutrophil activity.

**Methods/design:**

The EME-TIPAC trial is a double-blind, placebo-controlled, randomised, multicentre clinical trial.

A total of 330 symptomatic patients, aged 40 years old or older, with IPF diagnosed by a multidisciplinary team (MDT) according to international guidelines and a FVC ≤ 75% predicted will be enrolled. Patients are randomised equally to receive either two tablets of co-trimoxazole 480 mg or two placebo tablets twice daily over a median treatment period of 27 (range 12–42) months. All patients receive folic acid 5 mg daily whilst on the trial IMP to reduce the risk of bone marrow depression.

The primary outcome for the trial is a composite endpoint consisting of the time to death, transplant or first non-elective hospital admission and will be determined from adverse event reporting, hospital databases and the Office of National Statistics with active tracing of patients missing appointments. Secondary outcomes include the individual components of the primary outcome, (1) King’s Brief Interstitial Lung Disease Questionnaire, (2) MRC Dyspnoea Score, (3) EQ5D, (4) spirometry, (5) total lung-diffusing capacity and (6) routine sputum microbiology. Blood will be taken for cell count, biochemistry and analysis of biomarkers including C-reactive protein and markers of disease.

The trial will last for 4 years. Recruitment will take place in a network of approximately 40 sites throughout the UK (see Table 1 for a full list of participating sites). We expect recruitment for 30 months, follow-up for 12 months and trial analysis and reporting to take 4 months.

**Discussion:**

The trial is designed to test the hypothesis that treating IPF patients with co-trimoxazole will increase the time to death (all causes), lung transplant or first non-elective hospital admission compared to standard care (https://www.nice.org.uk/guidance/cg163), in patients with moderate to severe disease.

The mechanistic aims are to investigate the effect on lung microbiota and other measures of infection, markers of epithelial injury and markers of neutrophil activity.

**Trial registration:**

International Standard Randomised Controlled Trials Number (ISRCTN) Registry, ID: 17464641. Registered on 29 January 2015.

**Electronic supplementary material:**

The online version of this article (10.1186/s13063-018-2453-6) contains supplementary material, which is available to authorized users.

## Background

Idiopathic pulmonary fibrosis (IPF) is a specific form of chronic, progressive fibrosing interstitial pneumonia of unknown cause occurring in adults. At 7.44 per 100,000 person years [1], the incidence of IPF is similar to subarachnoid haemorrhage, ovarian cancer, leukaemia or mesothelioma [1, 2]. Current therapies are of limited efficacy and international guidelines only give them conditional support [3]. Immunosuppressive therapy is no longer advised [4], and the initial claims of the beneficial effects of *N*-acetyl cysteine [5] have not been substantiated when given as monotherapy [6]. Warfarin reduced mortality in an open-label trial but not in a placebo-controlled trial [7]. Pirfenidone [8, 9] and nintedanib [10, 11] reduce the rate of decline in lung function, with suggestions of increased survival [12].

Shulgina et al. [13] investigated the role of co-trimoxazole in patients with IPF (TIPAC trial). Co-trimoxazole 960 mg twice daily for 12 months was evaluated in 181 patients with idiopathic interstitial pneumonia (IIP), 166 of whom had IPF. Although there was no effect on forced vital capacity (FVC) (primary endpoint), co-trimoxazole was cost-effective in the intention-to-treat (ITT) analysis from a National Health Service (NHS) perspective in terms of incremental cost per quality-adjusted life years (QALYs) gained. In a per-protocol (PP) analysis, the co-trimoxazole-treated group demonstrated significant reductions in mortality compared to placebo (3/53 versus 14/65, odds ratio 0.21, 95% CI 0.06 to 0.78, *p* = 0.02), had improvements in QALYs and reduced the need for oxygen therapy. The findings were similar when confined to participants with IPF and were not influenced by baseline immunosuppressive therapy. The results were even more striking when considering patients with impaired lung function. Amongst patients with an FVC ≤ 75% of predicted normal (% predicted) there was a close to significant (*p* = 0.053) treatment effect.

As the pathogenesis of IPF is unknown the potential mechanisms of action of co-trimoxazole are uncertain. Co-trimoxazole is a broad-spectrum antibiotic with bactericidal effects against respiratory pathogens and the role of infection in IPF is becoming more evident [14]. However, it may have non-antimicrobial effects, targeting cellular processes that have been implicated in the pathogenesis of IPF. An evaluation of efficacy by a clinical trial that is adequately powered to detect clinically important differences on clinically relevant endpoints is required before this treatment can be considered in clinical practice.

The Efficacy and Mechanism Evaluation of Treating Idiopathic Pulmonary fibrosis with the Addition of Co-trimoxazole (EME-TIPAC) trial is designed to test the hypothesis that treating IPF patients with co-trimoxazole will increase the time to death (all causes), lung transplant or first non-elective hospital admission compared to standard care, as defined by the National Institute for Health and Care Excellence (NICE) guidelines [15], in patients with moderate to severe disease (FVC ≤ 75% predicted). Secondary objectives are to compare the clinical efficacy of this intervention in terms of respiratory-related hospital admission, death, health-related quality of life, QALYs, cough score and quality of life, lung function and oxygen saturations. Secondary mechanistic aims are to investigate the effect on (1) the lung microbiota and other measures of infection, (2) markers of epithelial injury and (3) markers of neutrophil activity. An exploratory aim is to determine whether the mechanistic properties are related to clinical efficacy.

## Methods/design

The trial is a phase III, double-blind, parallel-group, 1 to 1 randomised, placebo-controlled, multicentre clinical superiority trial of orally administered co-trimoxazole versus placebo in patients with moderate to severe (FVC ≤ 75% predicted) IPF, with outcomes assessed over a median treatment period of 27 (range 12–42) months. Participants receive co-trimoxazole or placebo until they meet a primary endpoint event, they withdraw consent, or the trial concludes. This trial is designed to align with routine care as much as possible and the trial visits are intended to coincide with routine clinical follow-up visits. Follow-up of assessment measures will continue for the duration of the trial for those participants stopping trial medication due to adverse events or patient choice. The vital status and details of admission to hospital will be captured for all patients who have consented to participate in the trial regardless whether they have withdrawn from the intervention or trial assessments.

Figure 1 provides a study flowchart of the trial design and Fig. 2 provides the time and event schedule. The trial protocol (v3.0, dated 16 May 2016) is based on the Standard Protocol Items: Recommendations for Interventional Trials (SPIRIT) 2013 Statement for protocols of clinical trials (see Additional file 1).

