### Interventions

Participants receive co-trimoxazole (generic) 960 mg as two tablets of 480 mg twice a day plus folic acid 5 mg once a day or placebo tablets (manufactured to appear identical to co-trimoxazole 480 mg) two oral tablets twice a day plus folic acid 5 mg once a day over a median treatment period of 27 (range 12–42) months. This is dispensed 3-monthly for the first 6 months then 6-monthly and supplied in bottles providing 1 month’s supply either by hospital pharmacy or via a courier. Participants are advised to store their medication below 25 °C but there will be no temperature monitoring after dispatch to the patient. Folic acid must be taken by participants whilst on the trial drug to reduce the risk of bone marrow depression associated with the long-term use of co-trimoxazole.

The trial drug may be reduced to two tablets once a day three times a week plus 5 mg folic acid once a day three times a week if patients develop gastrointestinal adverse effects or rash, have grade 1 hyperkalaemia (serum potassium > 5.0 mmol/L and < 5.5 mmol/L) or any other adverse event that, in the opinion of the local investigator, requires a dose reduction. In such cases, the dosing interval is to ensure that the dosing is spread throughout the week (e.g. Monday, Wednesday and Friday or equivalent). Once a patient has had their dose reduced, no re-escalation will be permitted, even if the adverse event leading to the reduction resolves.

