### Secondary outcomes

The individual components of the primary outcome: time to death (all causes) or transplant and time to first non-elective hospital admission will be analysed separately as secondary outcomes. In addition, respiratory-related events will be analysed separately from non-respiratory-related events. The following measurements will also be undertaken at baseline, 3 and 6 months post randomisation, then 6-monthly for the duration of the trial plus at the end of trial/hospitalisation.

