### Sample size

With 264 patients predicted to be randomised over a period of 30 months and an additional 12-month follow-up after the last patient is recruited (a total of 42 months after the first patient is enrolled, median patient trial duration of 27 months) we expect 96 primary endpoint events to occur uniformly over the duration of the trial. This will have 80% power (two-sided test, significance level of 5%) to show a change in hospitalisation-free survival from a median value of 28.8 months in the control arm to 51.1 months in the co-trimoxazole arm (hazard ratio of 0.56) using a log-rank test. This is based on a sensitivity analysis of all patients from TIPAC (including IIP and/or IPF) with reduced lung function (FVC < 75% predicted) using an intention-to-treat analysis.

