### Statistical analysis

All analyses will be conducted according to a detailed statistical analysis plan. Analyses will be adjusted for site and the use of baseline, licensed medication for IPF. The analysis populations are defined as intention-to-treat (all randomised individuals regardless of adherence), per-protocol (all randomised individuals who adhere to the trial medication to within 80% (based on pill counts)), modified-per-protocol (all randomised individuals who adhere to the high-dose regimen) and safety population (all patients randomised who received at least one dose of the trial treatment). Non-compliance will be dealt with using a Compliance-Adjusted-Causal-Effect (CACE) analysis, using compliance data from returned medication (pill counts).

The primary outcome will be analysed using a Cox proportional hazards model adjusted for the variables included in the minimisation algorithm (baseline licensed IPF medication and site). The results will be presented as the Kaplan-Meier estimate of the survival function for each treatment arm separately and, if appropriate, the median will be estimated. The treatment effect size will be the hazard ratio and estimated with 95% confidence intervals and *p* values.

At each relevant time point from 6 weeks post randomisation, the K-BILD, EQ5D, LCQ, spirometry (FVC per cent predicted, FEV per cent predicted, FVC absolute value, FEV absolute value and FVC/FEV ratio) and DLCO will be analysed using linear model to compare the average values between the treatment arms adjusted for the variables included in the minimisation algorithm: baseline disease-modifying therapy and site will be included as a random effect. The effect size will be the mean difference and will be presented with 95% confidence intervals and *p* values.

The MRC Breathlessness Score and cough score will be analysed using a Mann-Whitney test to compare the distribution of the score between the treatment arms. A generalised effect size will be estimated and presented with 95% confidence intervals and *p* values.

The safety analysis will be based on the pre-defined population (as above). Summary tables will be presented for incidence rates (number of patients with at least one incidence) of adverse events and serious adverse events coded according to the Medical Dictionary for Regulatory Activities (MedDRA). Tables of change from baseline will be presented for the blood and other clinical laboratory assessments.

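### The stated treatment period of 27 (range 12–42) months is potential follow-up; because trial drug stops at the first primary event, expected median time on drug is about 20 to 22 months at most

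*Protocol article*

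**What the plan says.** Methods/design describes a trial "with outcomes assessed over a median treatment period of 27 (range 12–42) months" and, in its next sentence, gives the rule for ending treatment: "Participants receive co-trimoxazole or placebo until they meet a primary endpoint event, they withdraw consent, or the trial concludes". Under Primary outcomes, the primary event is death, transplant or a first non-elective admission.

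Interventions repeats that tablets are taken "over a median treatment period of 27 (range 12–42) months", and the Abstract says the same. Sample size uses the same number under a different name, "median patient trial duration of 27 months", and shows where it comes from: "With 264 patients predicted to be randomised over a period of 30 months and an additional 12-month follow-up after the last patient is recruited". It expects 96 primary events and assumes event-free medians of 28.8 months (control) and 51.1 months (co-trimoxazole).

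Two further statements bear on how results will be read:

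- **Secondary outcomes:** "time to death (all causes) or transplant and time to first non-elective hospital admission will be analysed separately as secondary outcomes". Methods/design adds that vital status and admissions are captured for every consenting patient, including those who have come off the intervention.
- **Statistical analysis:** safety is summarised as "incidence rates (number of patients with at least one incidence) of adverse events", in everyone who took at least one dose.

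**The concern.** A treatment period cannot equal the full potential follow-up when treatment ends at an event that a large share of patients is expected to have. For 27 (12–42) months to be time on drug, nobody could have a primary event or stop early before the trial closes, yet the design rests on 96 events.

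A reader who takes the article at its word will think that half the participants receive the drug for more than 27 months and that all receive it for at least 12. That overstates the exposure behind the safety table. It also hides the fact that follow-up for death continues after the drug has stopped. And if co-trimoxazole delays primary events, patients on it stay on treatment longer, so raw counts of patients with an adverse event rest on more exposure in that arm.

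**Working it through.** **Inputs, all from Sample size unless noted.** Accrual 30 months; further follow-up 12 months; medians 28.8 and 51.1 months; 96 events; 264 patients in the calculation; 330 to be randomised (Methods/design); 1:1 allocation. My assumptions: exponential event times, uniform accrual and, at first, no stopping other than at a primary event or trial end.

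**1. The plan's own figures reproduce.**
- Follow-up: the first patient has 30 + 12 = 42 months available and the last has 12. Under uniform accrual, potential follow-up is uniform on 12–42 months, with median (12 + 42)/2 = 27. The stated 27 (12–42) is therefore exact as potential follow-up.
- Events: HR = 28.8/51.1 = 0.5636, with log −0.5734. Schoenfeld: 4 × (1.960 + 0.842)²/0.5734² = 95.5, so 96 events. This agrees with the article.

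**2. Time on drug under the stopping rule.** Time on drug is the smaller of time to primary event and potential follow-up. The probability of still being on drug at month t is

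P(t) = exp(−λt) × G(t), with G(t) = 1 for t < 12 and (42 − t)/30 for 12 ≤ t ≤ 42.

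λ = ln 2/28.8 = 0.02407 per month (control) and ln 2/51.1 = 0.01356 (co-trimoxazole). Setting P(t) = 0.5:
- Control: t = 18.56; 0.640 × 0.781 = 0.50.
- Co-trimoxazole: t = 21.83; 0.744 × 0.672 = 0.50.
- Pooled: t = 20.19; average of 0.615 and 0.760 is 0.688, and 0.688 × 0.727 = 0.50.

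At 27 months, P = 0.5 × exp(−27λ): 26% of control and 35% of active patients are still on drug, not 50%.

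**3. The lower limit of 12 months.** The probability of a primary event before month 12 is 1 − exp(−12λ): 25% (control) and 15% (active). Those patients are on drug for less than 12 months.

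**4. Mean time on drug by arm.** This is the area under P(t):
- Control: 10.42 (months 0–12) + 8.96 (months 12–42) = 19.4 months.
- Co-trimoxazole: 11.07 + 11.18 = 22.3 months.

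The ratio is 22.25/19.38 = 1.15. With no treatment effect the two means are equal.

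**5. Sensitivity of the pooled median.** The stated medians imply event probabilities of 0.466 and 0.302, so 132 × (0.466 + 0.302) = 101 events in 264 patients, slightly more than 96. I therefore also fitted one common hazard to 96 events.

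| Scenario | Median time on drug (months) |
|---|---|
| Stated medians, no other stopping | 20.2 |
| 96 events in 264 patients | 20.6 |
| 96 events in 330 patients | 22.0 |
| Stated medians, early stopping at 10 per 100 patient-years (assumed) | 17.8 |
| Stated medians, early stopping at 20 per 100 patient-years (assumed) | 15.8 |

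The article gives no early-stopping rate; the last two rows show a range only. No scenario reaches 27.

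**The case against.** The strongest reply is that this is a matter of labelling. The Sample size section names the 27 months correctly and shows its origin, and no calculation uses it as time on drug. The 96 events reproduce, and the primary analysis is untouched because the drug stops only at the primary event itself. All of that stands, and it limits the point to a wrong description of exposure and what follows from it for reporting.

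A second reply is that counting patients with at least one event is a conventional safety summary, that exposure is equal by arm if the drug has no effect, and that the 15% difference appears only at the full design effect. That is also true. But the article itself fixes the measure, and a rate per patient-year on treatment adds to it without displacing it.

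Three stronger readings are tempting, and the documents do not support them:

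- **That follow-up for death is unequal by arm.** It is not: vital status is captured for all who consented. Time to death or transplant, analysed by intention to treat, is a valid treatment-policy comparison that includes time after the drug has stopped. Per-protocol and compliance-adjusted analyses are also planned.
- **That adverse-event counts include time off drug after a primary event.** Nothing in the article says so. Continued assessment off drug is stated only for patients who stop because of adverse events or by choice, and the collection window may be in the full protocol.
- **That the share of deaths occurring off drug can be quantified.** This would need the proportion of first events that are deaths, the death hazard after admission, and whether any drug effect persists after stopping. The article gives none of these.

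**Conclusion.** The point holds as an internal contradiction in how exposure is described. Potential follow-up of 27 (12–42) months is called the treatment period in three places, while the stopping rule in Methods/design makes that impossible under the design's own event assumptions. Expected median time on drug is about 20 to 22 months before any other discontinuation, roughly 5 to 7 months below the stated figure, and the 12-month minimum fails for about one patient in four on control and one in seven on co-trimoxazole. These sizes rest on exponential event times and uniform accrual; early stopping would lower them further.

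The consequence for analysis is limited to safety reporting, where time on drug would differ by arm if the drug works. The contradiction does not affect the primary comparison, its event target or the validity of the mortality comparison. It is worth correcting because the figure is prominent and the correction is cheap.

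**What to change.** - Reconcile the Abstract, Methods/design and Interventions with the stopping rule: call 27 (range 12–42) months potential follow-up, as Sample size in effect does, and give expected median time on drug separately (about 20 to 22 months before other discontinuation, with the assumptions stated).
- In Secondary outcomes or Statistical analysis, note that time to death or transplant is a treatment-policy comparison that includes time after drug stop, with equal observation by arm.
- Report adverse events per patient-year on treatment beside the number of patients with at least one event.

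The cost is wording in three places, one sentence on the mortality outcome and one extra column in the safety table. The stated exposure becomes shorter and so looks less favourable. The stopping rule itself is a clinical matter, and no change to it is proposed.

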**Fig. 1 Fig1:**
[figure not shown]
Flow diagram of study design

**Fig. 2 Fig2:**
[figure not shown]
Time and event schedule

The trial is set in UK secondary-care centres that either meet the specifications required for specialist interstitial lung disease (ILD) centre status or work in association with specialist centres. The first patient was randomised on 15 May 2015. In total, 330 patients will be randomised into the trial. The trial has ethical approval from Surrey Borders Research Ethics Committee (reference 14/LO/1800) and is registered onto a clinical trial database (International Standard Randomised Controlled Trials Number 17464641). The Norfolk and Norwich University Hospital NHS Foundation Trust (NNUH) is the trial sponsor and has delegated responsibility for the overall management of the trial to the chief investigator and Norwich Clinical Trials Unit (NCTU), including the trial design, coordination, monitoring and analysis and reporting of results. A Trial Management Group (TMG) has been set up to assist with developing the design, co-ordination and strategic management of the trial. An Independent Trial Steering Committee (TSC) and Independent Data Monitoring Committee (DMC) have also been set up to provide advice to the NCTU on all aspects of the trial and safeguard the interests of trial patients. Membership of the TMG, TSC and DMC is detailed in Table 2.

**Table 1 Tab1:** Participating sites

Trust name	Principal investigator
Norfolk and Norwich University Hospitals NHS Foundation Trust	[name]
Papworth Hospital NHS Foundation Trust	[name]
Royal Brompton and Harefield NHS Trust	[name]
Sheffield Teaching Hospitals NHS Foundation Trust	[name]
University Hospital Birmingham NHS Foundation Trust	[name]
Heart of England NHS Foundation Trust	[name]
University Hospitals of North Midlands NHS Trust	[name]
North Bristol NHS Trust	[name]
Cardiff and Vale University Health Board	[name]
The Newcastle Upon Tyne Hospitals NHS Foundation Trust	[name]
Gateshead Health NHS Foundation Trust	[name]
Salford Royal NHS Foundation Trust	[name] [name]
University Hospital of South Manchester NHS Foundation Trust	[name]
Aintree University Hospitals NHS Foundation Trust	[name]
Lancashire Teaching Hospitals NHS Foundation Trust	[name]
Aberdeen Royal Infirmary	[name]
NHS Greater Glasgow and Clyde	[name]
Peterborough and Stamford Hospitals NHS Foundation Trust	[name]
Oxford University Hospital NHS Foundation Trust	[name]
Imperial College Healthcare NHS Trust	[name]
NHS Tayside	[name]
